## Results

Not applicable; this protocol paper does not contain any data in any form. Future papers will disseminate the study's results in line with the outcomes stated.

## Discussion

While research into PT for OCD remains in its early stages, substantial evidence suggests that it may effectively address the condition's behavioural patterns in nuanced and beneficial ways. Psilocybin has demonstrated the ability to enhance neuroplasticity and cognitive flexibility, alongside its potential to recalibrate metacognition. This recalibration could help individuals revise overly pessimistic, rigid beliefs tied to their specific OCD themes and beyond, allowing new evidence to reshape their perceptions more accurately. Such a shift could directly ameliorate OCD symptoms, as condition is characterised by compulsive rituals designed to prevent a perceived 'worst-case' scenario and the intense emotional distress associated with it.

Although the effects of psychedelics on the cognitive tasks included in PsilOCD have not been directly studied in humans, it is worth exploring whether psilocybin can improve cognitive performance in individuals with OCD, especially if these improvements align with clinical symptom reduction. If the low-to-moderate 10 mg dose of psilocybin under investigation is effective in alleviating OCD symptoms, it could emerge as a powerful complement to therapy. And examining its impact on neuroplasticity and cognition will yield valuable insights into how psilocybin might influence the core obsessive-compulsive machinery. Given the multifaceted and interconnected nature of OCD, advancing our understanding of how novel treatments may selectively target and disrupt specific elements of its cyclical patterns represents a crucial step toward more effective interventions.

## Conclusions

By publishing the study protocol, we aim to improve methodological transparency, rigour, and accountability and subsequently contribute towards more impactful outcomes. This study will investigate the effect of psilocybin on neural mechanisms in an OCD population, representing the first study exploring the impact of psychedelics on OCD in the UK. It is important to note that the small sample size of up to 20 completers, while typical for early-stage feasibility studies, inherently limits the statistical power of the results and, consequently, their generalisability. However, such studies remain invaluable for generating preliminary insights into efficacy and tolerability, identifying patterns in individual responses, and refining hypotheses to guide the design of larger-scale clinical trials.

The results will reveal whether a low-moderate dose of psilocybin improves clinical OCD symptoms, and whether this correlates with changes in the underlying cognitive features of OCD, neuroplasticity levels, BDNF serum levels, and inflammatory mediators. Consequently, the findings from PsilOCD have the potential to evaluate the potential of psilocybin for OCD, inform larger, randomised clinical trials, and, if the results are promising, pave the way for making this treatment accessible to patients.

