## Abstract

Background: Obsessive-compulsive disorder (OCD) is a complex condition marked by persistent distressing thoughts and repetitive behaviours. Despite its prevalence, the mechanisms behind OCD remain elusive, and current treatments are limited. This protocol outlines an investigative study for individuals with OCD, exploring the potential of psilocybin to improve key components of cognition implicated in the disorder. The PsilOCD study strives to assess the effects of low-moderate psilocybin treatment (10 mg) alongside non-interventional therapy on several facets of OCD. The main focus points of PsilOCD are cognitive flexibility, measured with cognitive tests, and neuroplasticity, assessed through electroencephalography (EEG).

Methods: 20 blinded participants with OCD will complete two dosing sessions, separated by four weeks, where they will receive 1 mg of psilocybin on the first and 10 mg on the second. The first dose serves as an active placebo, and the latter is a low-moderate dose that induces relatively mild-moderate emotional and perceptual effects. Participants will be supported by trained psychedelic therapists, who will sit with them during each dosing session and provide virtual preparation and integration sessions over the 12-week study period. Therapeutic support will be the same for both the 1 mg and 10 mg sessions. PsilOCD’s primary outcomes include scores in the intradimensional-extradimensional (ID-ED) shift task, which is an established measure of cognitive flexibility, and neuroplasticity as quantified by a visual long-term potentiation (vLTP) task. This task is delivered as part of an EEG paradigm and measures acute quantified changes in neuroplasticity in the brain’s visual system. The ID-ED task will be conducted twice, two days after each dosing session, and the EEG recordings will also be taken twice, immediately after each session. Secondary outcome assessments will include OCD and affective symptom severity, as well as an array of patient-reported outcome measures (PROMs), in the form of questionnaires designed to assess well-being, dissociable and well-established mood-related (affective) measures, and participants’ subjective experience of the psilocybin experience.

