Discussion: This study’s results are expected to offer critical insights into the neural mechanisms underlying the effects of psilocybin-assisted therapy in treating OCD, and whether these correlate with changes in the cognitive features of the condition. As a secondary aim, it will ascertain whether a low, tolerable dose is a feasible and efficacious clinical treatment, and will provide crucial data to guide the design of a potential follow-up randomised control trial (RCT).

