In the most recent study by Moreno et al., participants saw a notable drop in their Y-BOCS scores, and adverse reactions or heightened anxiety related to the psilocybin were not reported. These findings suggest that the therapeutic potential of low doses of psilocybin for OCD may be linked to activating the 5-HT2A receptor within the relevant brain circuitry. Notably, the three highest doses all yielded significant improvements, implying that a low dose of psilocybin (10 mg, comparable to the lower 0.1 and 0.2 mg/kg doses administered by Moreno et al.) may be a viable treatment [54]. This is useful to determine, since many OCD patients fear loss of control and may be opposed to having a more intense psychedelic experience. Most studies assessing psilocybin in the context of mental health have explored 25 mg doses [48,58]. However, if meaningful improvements in OCD symptoms can arise from the administration of 10 mg, this may be preferable to many patients.

Literature suggests that 1 mg of psilocybin serves as a good control, or active placebo [40,42,48]. This dose falls at the lower limit of what is typically regarded as a 'microdose', and does not produce noticeable physiological, perceptual, or emotional effects [43,59]. Importantly, opting for a 1 mg dose rather than an inert placebo also enables better blinding, as all patients can be told that they will be given ‘up to 10 mg’ of psilocybin during each session. This decreases the chance of a ‘disappointment effect’ from the 1 mg dose, mitigating the risk of participants believing that they have been given no psilocybin during the first dosing session and responding emotionally. Participants should be given the same therapeutic support before, after, and during both dosing days.

How psilocybin might improve the nuanced, dissociable cognitive deficits of OCD

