Participants will complete study activities at 13 time points over the 12-week study period after screening, of which two are in-person dosing days (see Figure 1 for the schedule). Two trained therapists (or ‘guides’) will accompany participants and provide psychotherapeutic support throughout the duration of the study (more information in the section below). Participants will attend two dosing days and receive 1 mg of psilocybin on the first (active placebo) and 10 mg on the second. Dosing sessions are separated by at least four weeks, each preceded by at least one preparation session and followed by four integration sessions, with the final integration session coming four weeks after the final dosing session.

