**Figure 1 FIG1:**
[figure not shown]
A depiction of the PsilOCD study timeline: the total period from the first preparation session (Prep. 1) to the final integration session (Int. 4). EEG: Electroencephalography; ECG: Electrocardiogram; MINI: Mini-International Neuropsychiatric Interview

Preparation

Preparatory sessions serve to initiate the self-reflective therapeutic process, build trust and rapport with the therapists, remind participants of what to expect from the dosing days, and start discussing themes that arise for them related to their OCD symptoms. Any changes in participants’ symptoms, well-being and attitude towards the study are documented. Preparatory sessions occur one week and one day before each Dosing Day.

Dosing Day 1 and 2

The participant will arrive at the clinic (Central and North West London (CNWL)-Imperial Psychopharmacology & Psychedelic Research (CIPPRes) Clinic, at CNWL NHS Trust’s St Charles Hospital) in the morning, and will be administered psilocybin (1 mg on the first visit and 10 mg on the second). The therapists will offer non-directive psychological support throughout the dosing days. One hour after the substance wears off, the EEG vLTP paradigm will be carried out to quantify enhancements in plasticity. Bloods will be taken and tested for BDNF levels, as well as immune markers. The participant’s subjective experience will also be assessed using questionnaires (the Mystical Experience Questionnaire (MEQ), the Challenging Experience Questionnaire (CEQ) and the Emotional Breakthrough Inventory (EBI)), and they will be prompted to estimate the dose of psilocybin that they received. This day will end at approximately 17:30, at which point they will be driven home in a taxi or collected by a trusted contact.

Integration

The participant will attend three integration sessions with the therapists, designed to help them interpret any insights and apply them to their lives. These sessions will take place one day, one week and two weeks after each dosing day. The Y-BOCS will also be conducted again, as well as the aforementioned measures of affective symptoms.

Neuropsychological Task Performance (CANTAB Test Battery)

Study collaborators from the University of Cambridge will administer the CANTAB test battery remotely two days after each dosing session. This will involve ED-shift outcome measures using ID-ED Set Shift, Probabilistic Reversal Learning, and Paired Associates Learning task (a neutral control task).

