**Table 2 TAB2:** Summary of PsilOCD Outcome Measures and Hypotheses ID: Intradimensional; ED: Extradimensional; CANTAB: Cambridge Neuropsychological Test Automated Battery; EEG: Electroencephalography; vLTP: Visual long-term potentiation; Y-BOCS: Yale-Brown Obsessive Compulsive Scale; MADRS: Montgomery-Asberg Depression Rating Scale; PROM: Patient-reported outcome measure; BDNF: Brain-derived neurotrophic factor

Outcome Type	Outcome Measure	Hypothesis
Primary Clinical Outcome	Cognitive Flexibility: ID-ED Shifting (CANTAB)	Participants will show improved scores on the CANTAB ID-ED task two days after the 10 mg psilocybin dose compared to two days after the 1 mg dose.
Primary Neuroimaging Outcome	Neuroplasticity: EEG vLTP	Participants will demonstrate higher capacity for neural plasticity two hours post 10 mg dose compared to the 1 mg dose, as indicated by vLTP in EEG recordings.
Secondary Clinical Outcome	Y-BOCS and MADRS Scores	Y-BOCS scores for obsessions and compulsions are expected to decrease after the 10 mg dose but not after the 1 mg dose. MADRS scores will likely follow a similar pattern.
Secondary Clinical Outcome	Cognitive Inflexibility: Reversal Learning (CANTAB)	Participants will show improved scores in reversal learning two days post 10 mg psilocybin dose, but not two days post 1 mg dose.
Secondary Clinical Outcome	Cognitive Inflexibility: Paired Associates Task (CANTAB, Control Task)	Scores are expected to be comparable after both 1 mg and 10 mg doses, as visuospatial tasks should not be affected by 5-HT2A receptor modulation.
Secondary Clinical Outcome	Cognitive Inflexibility: Information-Seeking Task	If psilocybin reduces the rigidity of high-level priors, confidence will improve, and information-seeking behavior will reduce. Significant effects are expected one day after the 10 mg dose, not the 1 mg dose.
Secondary Clinical Outcome	Self-Reported Well-Being and Affective Measures (PROMs)	Compared to 1 mg, the 10 mg dose is expected to improve anxiety and depression-related symptoms, decrease impulsivity (Barratt Impulsivity Scale), increase openness, and decrease neuroticism (Big Five Inventory).
Secondary Clinical Outcome	Acute Subjective Experiential Measures (PROMs)	The 10 mg psilocybin dose will result in significantly higher scores on questionnaires assessing subjective drug effects compared to the 1 mg dose.

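### With a fixed dose order and no rater masking described, the Y-BOCS and MADRS data cannot carry the efficacy conclusions that the article announces

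*Protocol article*

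**What the plan says.** **Order and blinding.** The Abstract (Methods) says that "20 blinded participants with OCD will complete two dosing sessions", "where they will receive 1 mg of psilocybin on the first and 10 mg on the second". The Study visits section repeats the sequence: participants "receive 1 mg of psilocybin on the first (active placebo) and 10 mg on the second". No randomised or counterbalanced order is described. The Introduction argues that "opting for a 1 mg dose rather than an inert placebo also enables better blinding", and the reasoning there concerns what patients are told and believe. The breaking-of-blind question in Table 3 is listed among the patient-reported measures.

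**Symptom ratings.** Table 3 lists Y-BOCS and MADRS as clinician-rated, at video screening, V3, V7 to V9 (after the first dose) and V13 to V15 (after the second). The Integration section, which describes sessions following each dosing day, adds: "The Y-BOCS will also be conducted again, as well as the aforementioned measures of affective symptoms". The One-Month Follow-ups section also includes these ratings and says that the first follow-up is mainly preparation for the second dose; Table 3 labels that visit (V9) as Prep-3 too.

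**Hypothesis and analysis.** Table 2 states: "Y-BOCS scores for obsessions and compulsions are expected to decrease after the 10 mg dose but not after the 1 mg dose", with MADRS expected to behave similarly. Table 4 plans a linear mixed model testing a time-by-dose interaction.

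**Conclusions announced.** As a secondary aim, the Abstract (Discussion) says that "it will ascertain whether a low, tolerable dose is a feasible and efficacious clinical treatment". The Conclusions say: "The results will reveal whether a low-moderate dose of psilocybin improves clinical OCD symptoms". The limitation conceded there is the small sample, with its effect on power and generalisability.

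**The concern.** Two separate problems bear on the same symptom contrast.

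- **Detection bias.** With a fixed order, anyone who knows the visit knows the dose. The ratings fall at visits tied to a particular dosing day, and the direction of the hypothesis is published. If the rating clinician knows the visit, expectation can act on the score in the hypothesised direction.
- **Confounding with period.** Whatever the rater knows, all 10 mg ratings come later than all 1 mg ratings. Natural course, accumulated therapeutic support, familiarity with the setting and any carry-over from the first dose all lie on the same axis as dose.

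Neither problem is one of precision, so conceding a small sample does not cover them, and a larger sample would not remove them. At stake is what the trial may conclude about symptoms, and whether a possibly inflated Y-BOCS effect is carried into the follow-up randomised trial, which would then be planned too small.

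**Working it through.** The plan gives no alpha, power, SD or expected effect for Y-BOCS or MADRS, so there is no figure to reproduce. The check is mainly a reading of the text, followed by an illustration of scale.

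**1. Does visit determine dose?** The order is the same for everyone (Abstract, Study visits, Dosing Day 1 and 2). V7 to V9 are therefore always after 1 mg and before 10 mg, and V13 to V15 always after 10 mg. V9 doubles as preparation for the second dose, so the content of that visit shows that the second dose is still to come.

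**2. Is rater masking described?** No. The blinding rationale, the information given about dose and the blinding check all concern the participant. The article does not say who rates Y-BOCS and MADRS after dosing, nor whether that person is masked to visit.

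**3. Would masking be enough?** No. Dose and period are the same variable here. A model with time and dose terms cannot tell 10 mg from the second period, because no participant has 10 mg first.

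**4. Do the stated conclusions allow for this?** The Abstract and Conclusions sentences state that efficacy will be determined. The limitation attached is sample size; fixed order and rater knowledge are not listed.

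**5. Illustration of scale (assumptions, not figures from the documents).** Take a two-sided paired t-test at 0.05 with n = 20, so df = 19 and critical t = 2.093. Suppose there is no true dose effect and a systematic rating shift of b points, with SD s of the paired difference. The noncentrality is (b/s) × √20, and the false-positive probability is the noncentral-t probability beyond ±2.093. With b = 2 and s = 5, for example: 0.4 × 4.472 = 1.789, which gives 0.397.

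| Assumed bias b | s = 5 | s = 6 | s = 8 |
|---|---|---|---|
| 1 point | 0.136 | 0.109 | 0.083 |
| 2 points | 0.397 | 0.294 | 0.186 |
| 3 points | 0.721 | 0.565 | 0.357 |

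The smallest observed standardised difference that reaches significance is 2.093/√20 = 0.47. The same arithmetic applies to a period shift of equal size. This is not the planned analysis: how a bias would enter the time-by-dose interaction depends on coding that the article does not give. The table shows only that a modest systematic shift could pass for an effect at this sample size.

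**The case against.** A reader might infer that every Y-BOCS and MADRS rater knows the dose. The documents do not establish that. Calling participants blinded does not say that raters are unblinded. The Integration sentence is passive and names no rater. Table 3 places a Y-BOCS at the video screening, a call that the Screening and consent section gives to a psychiatrist, so the guides need not be the raters. Rater arrangements are also something an article may leave to the full protocol. This stands: rater knowledge can be raised only conditionally, and its absence from the article is not in itself a fault.

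The wording has softer surroundings. The Abstract sentence is introduced as a secondary aim and ends with guiding a possible follow-up trial. The Conclusions also speak of preliminary insights and of informing larger randomised trials, and the study is described as a feasibility study. This stands in part: the overall tone is modest, but the two sentences at issue remain unconditional.

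Both primary outcomes in Table 2 are a computerised cognitive task and an EEG measure, so this point about clinician ratings does not reach them. That stands.

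Self-rated scales already bypass the rater: PHQ, SDS and STAI-T are taken at all six post-dose rating visits. That also stands, but those listed are affective or disability measures. CAIOC-13 is the obsessionality measure available at the one-month visit after each dose.

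Asking for masked raters would be a weak remedy. A clinician who sees the same participant repeatedly can count visits, the documents show no spare staff, and period confounding would remain. This stands, so masking is not the requested change.

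**Conclusion.** The concern holds in a limited form. A fixed-order design with no rater masking described cannot support a conclusion that 10 mg is efficacious or improves OCD symptoms. That follows from the order alone, whoever rates. Rater expectation is a further possible source of bias, in the hypothesised direction, unless the full protocol masks raters to visit.

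The documents do not allow the size of any bias to be estimated. Under the assumptions in the table, a 1-point shift gives 8% to 14% false positives, 2 points 19% to 40% and 3 points 36% to 72%, against a nominal 5%. These figures rest on assumed bias and SD values and on a simple paired t-test, and should not be read as the error rate of the planned mixed model. Nor do they show that the symptom effect will be overestimated, only that it could be.

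The consequence is confined to secondary outcomes and to what is claimed from them. It matters because those data are meant to inform the follow-up randomised trial.

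**What to change.** 1. **Reword the two statements** in the Abstract (Discussion) and the Conclusions. Present Y-BOCS and MADRS changes as exploratory, fixed-order estimates for planning the follow-up randomised trial that do not establish efficacy.
2. **Extend the stated limitations.** Beside sample size, name the fixed order (confounding with time, repeated support and carry-over) and, unless raters are masked to visit, rater knowledge of dose. If the full protocol does mask raters, one sentence saying so settles that part. The fixed-order limitation remains either way.
3. **Report CAIOC-13 beside Y-BOCS.** It is self-rated and already scheduled at V2, V9 and V15, so it gives one reading before dosing and one about a month after each dose without passing through the rater. State that it remains open to participant expectancy and period effects.

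The cost is a few sentences, one extra table and a weaker stated symptom claim. No visit, instrument or dosing arrangement changes.
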